## Abstract

**Background:**

IQ deficits are linked to even mild obstructive sleep apnoea (OSA) in children. Although OSA is commonly first diagnosed in the pre-school age group, a randomised trial is still needed to assess IQ outcomes after adenotonsillectomy in the pre-school age-group. This randomised control trial (RCT) will primarily determine whether adenotonsillectomy improves IQ compared to no adenotonsillectomy after 12 months, in preschool (3–5 year-old) children with mild to moderate OSA.

**Methods:**

This protocol is for an ongoing multi-centred RCT with a recruitment target of 210 subjects (105 in each arm). Children age 3–5 years with symptoms of OSA, are recruited through doctor referral, at the point of referral to the Ear Nose and Throat (ENT) services. Screening is initially with a questionnaire (Paediatric Sleep Questionnaire, PSQ) for symptoms of obstructive sleep apnoea (OSA). Where questionnaires are positive (suggestive of OSA) and ENT surgeons recommend them for adenotonsillectomy, they are invited to participate in POSTA. Baseline testing includes neurocognitive testing (IQ and psychometric evaluation with the neuropsychologist blinded to randomisation) and overnight polysomnography (PSG). Where the Obstructive Apnoea-Hypopnea Index (OAHI) from the PSG is <10/h per hour, consent for randomisation is sought; children with severe OSA (OAHI ≥ 10/h) are sent for immediate treatment and excluded from the study. After consent is obtained, participants are randomised to early surgery (within 2 months) or to surgery after a usual wait time of 12 months. Follow-up studies include repeat neurocognitive testing and PSG at 12 (with the waiting list group studied before their surgery) and 24 months after randomisation. Analysis will be by intention to treat. The primary outcome is IQ at 12 months’ follow-up.

**Discussion:**

If IQ deficits associated with OSA are reversible 12 months after adenotonsillectomy compared to controls, future clinical practice advise would be to undertake early surgery in young children with OSA. The study could provide data on whether a window of opportunity exists for reversing IQ deficits linked to OSA in the pre-school age-group.

**Trial registration:**

Australian and New Zealand Clinical Trials Registration Number ACTRN12611000021976.

## Background

Children with upper airway obstruction in sleep (obstructive sleep apnea, or OSA) may display repetitive, discrete episodes of airway obstruction associated with intermittent desaturation and arousal. However, they frequently also demonstrate long periods of partial airway obstruction associated with snoring, increased work of breathing and normal gas exchange in addition to the discrete events, or as their only expression of the disease.

Snoring reportedly affects 8–12% of children while 1–3% have OSA with discrete respiratory events [1]. Thus, even at its lowest prevalence, around 1 child in every primary school classroom has OSA, equating to 80,000 affected children in Australia and 16,000 children in New Zealand [2]. Although snoring and OSA are common across the childhood age-range, studies specific to the pre-school age group are vital. The first presentation of OSA is often in this age group, when the lymphoid tissue of the adenoids and tonsils is at its largest relative to the bony skeleton of the airway, thus compromising the upper airway size [3]. Adenotonsillar enlargement is the commonest treatable element of OSA in children and adenotonsillectomy (AT) constitutes the primary treatment intervention.

Polysomnography (PSG) is the standard investigation used to detect the presence and severity of OSA [4]. PSG studies provide an audio-visual assessment of obstruction and a documentation of the frequency of apneic events; defined as the number of obstructive apnoea & hypopnea events that occur per hour of sleep time. PSG outcomes thus provide the index of events per hour (OAHI), the severity of blood gas disturbances (hypoxia and hypercapnia), and the frequency of arousals. In the pediatric literature the severity of airway obstruction is then classified from PSG as on the basis of the obstructive apnoea-hypopnea index (OAHI).

### Neurocognitive associations with OSA

Recent studies show that snoring or mild OSA are associated cognitive and behavioral deficits in school-age children [5–14]. The mechanism of the association is not clear, and studies have examined associations with hypoxia, sleep fragmentation, and lack of cerebral blood flow adaptation as likely candidates [15–18]. Most human studies pertaining to recovery of neurocognitive function examine sequelae of traumatic or acute brain injury. Importantly, a number of those studies show that younger children generally have less capacity to compensate for brain injury than older children [19]. In contrast, some small studies suggest greater potential for recovery of specific neurocognitive processes in younger children [20].

To date, a substantial amount of the literature pertaining to neurocognition in children with OSA has come from studies in school-age children. The biggest cognitive impact of OSA is on children’s executive function. The development of the components of executive function is rapid in the age-range of 3–8 years, but continues through childhood and adolescence and is aligned with growth spurts and myelination in the frontal lobes [21]. Specific links have been suggested amongst sleep, behavioral problems, and executive function because of the prolonged developmental time frame of executive function in childhood, including the potential for there being a critical period of development [22]. Limited knowledge regarding the effects of age at the time of brain injury on subsequent IQ recovery means that results from studies of OSA in school-age children cannot be confidently extrapolated into the pre-school age group. Therefore, pre-school children are a vitally important group in which to investigate the adverse effects of OSA.

### Changes after treatment of OSA

The Childhood Adenotonsillectomy trial (CHAT) is a published randomized controlled trial in children evaluating IQ outcomes after adenotonsillectomy. Children in that study were school-age aged 5–9 years (*n* = 464), with 7 month follow up post intervention [23]. That study found no effect of early AT on attention or executive function as measured by neuropsychological testing. However the positive impacts of surgery included reduced symptoms and improved behavior, quality of life and PSG findings, so the authors concluded that the study provided evidence of the beneficial effects of early AT [23]. An editorial accompanying the publication of the CHAT study suggested that studies now need to focus on children at a younger age and with longer follow-up to evaluate whether IQ deficits are at all reversible [24].

## Aims

The POSTA (Pre-school OSA Tonsillectomy Adenoidectomy study) is a randomized, controlled trial of adenotonsillectomy in pre-school age children, with mild to moderate OSA, designed to evaluate neurocognitive outcomes after early adenotonsillectomy compared to watchful waiting, with a 12-month follow-up. Subjects will be assessed at baseline and again 12 months after randomization. Subjects randomized to the control group will have surgery following their 12 month follow-up assessment (approximating the average delay to surgery in Australia for children with this severity of OSA). Subjects randomized to intervention will have AT within 2 months of randomization. The specific aim is to determine whether AT improves IQ in preschool (3.0–5.0 year-old) children with mild to moderate OSA in a group who undergo early AT compared to those with no AT after 12 months. The design will allow us to test the principal hypothesis that IQ benefits will be demonstrable 12 months after surgery as opposed to no surgery in the pre-school age-group. Table 1 shows the primary and secondary outcomes to be measured.

**Table 1 Tab1:** Primary and secondary outcomes

Primary Outcome: Intellectual ability (IQ) as determined by the Woodcock-Johnson III (WJ-III) Test of Cognitive Abilities	
Secondary Outcomes:	
• Behavioral parameters (PRS-BASC-II)	
• Executive Function (BRIEF-P)	
• Parental Stress (Parental Stress Index)	
• Polysomnography (PSG) parameters	
• Sleep Symptoms (Pediatric Sleep Questionnaire- PSQ)	
• Anthropometry: change in height, weight, and BMI percentiles	
• Blood Pressure: Mean arterial pressure	
• Audiology	
• Quality of life	

## Design

### Overview of the study design

Pre-school age children (3.0–5.0 year-old) with a history of snoring will be contacted at the point of referral. The Pediatric Sleep Questionnaire (PSQ) will be used to screen for symptoms of OSA [25]. Children with a questionnaire score suggestive of OSA will be eligible for overnight sleep studies to classify the severity of their disease. Those with mild to moderate OSA (obstructive respiratory event index <10 per hour) are eligible for inclusion. Those with severe OSA (10 per hour) will be sent for immediate treatment and excluded. Recruited subjects will proceed to neurocognitive (IQ) testing and will then be randomized to either immediate or routine surgical waiting times. The neurocognitive tests (see details below) will apply to all participating children at baseline, then at 12- and 24-month follow-up. A routine surgical wait time for adenotonsillectomy means surgery 12 months after randomization, while early surgery will occur within 2 months of randomization. All children will have repeat neurocognitive testing 12 months after their randomization.

#### Recruitment strategy

Families referred to the hospital for adenotonsillectomy because of a history suggestive of OSA will be approached by mail for participation in this study. A letter, including the Pediatric Sleep Questionnaire (“PSQ”) questionnaire for OSA [25], will be sent to the families with a postage paid return envelope. Children with positive answers to ≥33% of the 22 question-items are considered to have a questionnaire diagnosis of OSA and will be invited to undergo overnight polysomnography (*PSG, see below for details*) to define the severity of their OSA. Questionnaire screening will ensure that children having PSG have high probability of OSA as this questionnaire has specificity of 0.87 for OSA in a general pediatric setting. After PSG children with an OAHI < 10 events/h will proceed to baseline testing while those with an OAHI >10 will require early clinical intervention and exclusion from further study.

#### Exclusion criteria

Children with medical conditions known to affect neurocognitive development (including hearing loss of >35 DB), previous tonsillectomy or airway surgery, high-risk genetic and craniofacial syndromes, identified neurodevelopmental conditions, cyanotic heart disease or previous cardiopulmonary bypass, and conditions that preclude neurocognitive testing or that preclude adenotonsillectomy will be excluded. Children with severe OSA (OAHI >10/h on sleep study) will also be excluded because they need to proceed to treatment to avoid morbidity from ongoing OSA. This group also has higher post-operative complication rates [26, 27]. Table 2 shows the list of inclusion and exclusion criteria.

**Table 2 Tab2:** POSTA eligibility and exclusion criteria

Inclusion Criteria:	
1. Children aged 3–5 years at the time of primary assessment for evaluation of snoring	
2. Deemed suitable for adenotonsillectomy on surgical evaluation	
3. Confirmed on PSG to have mild-moderate OSA, defined as OAHI < 10 events/h	
Exclusion Criteria:	
1. Medical conditions known to affect neurocognitive development (including hearing loss >35DB)	
2. Previous tonsillectomy or airway surgery	
3. High risk genetic and craniofacial syndromes	
4. Previously identified neurodevelopmental conditions	
5. Cyanotic heart disease or previous cardiopulmonary bypass	
6. Conditions that preclude neurocognitive testing or that preclude adenotonsillectomy	
7. Confirmed on PSG to have severe OSA, define as OAHI >10/h	

*PSG* polysomnography, *OAHI* obstructive apnoea hyponoea index

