#### Method of randomization

After completing initial questionnaire, sleep study and IQ assessments, children will be centrally randomized either to immediate surgery or to remain as waiting list controls. Study center and severity of OSA may all influence study outcomes. To avoid imbalance between the groups, these prognostic factors will be used for stratified randomization with OSA classified as < 5 events/h or > 5 events/h by center. To avoid small cell sizes we will implement a minimization algorithm to ensure that randomization groups are balanced for the stratifying variables. Centralized randomization is through the Children’s Hospital at Westmead. Each patient will be assigned a unique trial number that will be used for recording all their data. Protocols will be standardized between centers, including sleep study analysis, IQ testing, and surgical procedures.

*Intervention* will comprise adenotonsillectomy within 2 months of the assignment date. All children will undergo complete extra-capsular tonsillectomy and adenoidectomy, regardless of the size of the adenoids. The adenoidal bed will be visualized at the end of the procedure, to ensure the adenoidectomy is satisfactorily complete. It has been agreed that diathermy for adenoids is acceptable.

The main retention strategy will be 2-monthly phone contact with participant families, during which 5 questions will be asked about the child’s health.

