#### Sleep study concordance

As sleep studies will be carried out in 3 different sleep laboratories, a maximum of two experienced sleep technologists will be solely responsible for analysis of the PSG studies in each center. Analysis criteria have been agreed upon and those involved in analyzing studies will meet regularly to evaluate studies and ensure concordance. No published data exists on multi-center trial concordance for pediatrics.

The severity of OSA is defined by the number of obstructive apnoea & hypopnea events that occur per hour of sleep time expressed as the index of events per hour (OAHI). Standard diagnostic categories for pediatric OSA will be used and are: Primary Snoring <1 event/h; mild OSA 1–5 events/h; moderate OSA 5–10 events/h; and severe OSA >10 events/h [34]. Severe OSA experience nocturnal respiratory failure and severe desaturations, and there is clinical imperative for them to receive the beneficial effects of adenotonsillectomy [34–36].

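### Entry rule labels every OAHI below 10/h as mild-moderate OSA, although the protocol's own scale classes OAHI below 1/h as primary snoring, so the overall result will not be specific to mild-moderate OSA

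*Protocol article*

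**What the plan says.** Table 2 in the section Exclusion criteria gives inclusion criterion 3 as "Confirmed on PSG to have mild-moderate OSA, defined as OAHI < 10 events/h". Three other places state the same rule, again with an upper limit only:

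- Overview of the study design: "Those with mild to moderate OSA (obstructive respiratory event index <10 per hour) are eligible for inclusion".
- Recruitment strategy: "After PSG children with an OAHI < 10 events/h will proceed to baseline testing".
- Abstract, Methods: the OAHI "from the PSG is <10/h per hour, consent for randomisation is sought".

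The section Sleep study concordance says standard paediatric categories will be used and lists them: "Primary Snoring <1 event/h; mild OSA 1–5 events/h; moderate OSA 5–10 events/h; and severe OSA >10 events/h". No section sets a lower limit for entry, and none of the seven exclusion criteria removes a child with OAHI below 1/h.

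The Aims and the Abstract's Background name the population as preschool children with mild to moderate OSA. Outcomes and significance foresees a conclusion on the timing of surgery for that same group.

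**The concern.** The entry rule and the severity scale use the same PSG index and the same disease name but draw the group differently. By Table 2, mild-moderate OSA runs from 0 to below 10/h. By the severity scale it starts at 1/h, and the range below carries another name.

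The stake is what the primary result can be said to show. If children below 1/h are randomised, the intention-to-treat contrast averages over children with and without mild-moderate OSA as the protocol defines it. If surgery does less for IQ in the children below 1/h, a null overall result might partly reflect dilution. A positive result would be reported for mild to moderate OSA although it was estimated in a wider group. Because criterion 3 treats both kinds of child as one, nothing in its wording would alert a reader of the results.

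**Working it through.** **1. The text.** Take a child with OAHI 0.2/h, a positive questionnaire and a surgical recommendation.

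| Place | Rule | Result for this child |
|---|---|---|
| Table 2, inclusion criterion 3 | OAHI < 10/h | confirmed mild-moderate OSA, eligible |
| Overview; Recruitment strategy; Abstract | < 10/h | proceeds to testing and randomisation |
| Table 2, exclusion criterion 7 | OAHI > 10/h | not excluded |
| Sleep study concordance | < 1/h is primary snoring; mild OSA from 1/h | not mild or moderate OSA |

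The other entry conditions (age, at least 33% positive questionnaire items, surgical suitability) are not PSG criteria and do not set a lower OAHI limit.

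**2. The plan's own sample size.** Inputs from Sample size and power: difference 4 points, SD 8, power 0.90, significance 0.05 (taken as two-sided), equal arms.

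- Normal approximation: n = 2 × (1.960 + 1.282)² × 8² / 4² = 84.06, so 85 per arm.
- t-based: power is 0.8999 at 85 and 0.9032 at 86, so 86 per arm, as stated.
- Pocock step: the number of looks is not given. With two looks and an inflation factor of about 1.10 (both assumed), 1.10 × 85 = 93.5 and 1.10 × 86 = 94.6, consistent with 94.
- Follow-up: 94 / 0.9 = 104.4, so 105 per arm and 210 in total, as stated.

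The sample size reproduces. It supposes that the 4-point difference is the average over everyone randomised.

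**3. Conditional dilution.** Let f be the share with OAHI below 1/h and k the fraction of the 4-point gain that these children obtain. The average difference is 4 × (1 − f × (1 − k)). The document gives neither f nor k; the values below are assumptions. Power is for a two-sided 5% t test without interim looks, SD 8, 94 per arm. The standard error is 8 × √(2/94) = 1.167.

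| f | difference, k = 0 | power | difference, k = 0.5 | power |
|---|---|---|---|---|
| 0% | 4.0 | 93% | 4.0 | 93% |
| 10% | 3.6 | 87% | 3.8 | 90% |
| 20% | 3.2 | 78% | 3.6 | 87% |
| 30% | 2.8 | 67% | 3.4 | 83% |
| 40% | 2.4 | 53% | 3.2 | 78% |

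With no dilution, power is above the planned 90% because 94 already includes the Pocock allowance. Interim looks would lower every figure somewhat.

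**4. Precision of an analysis restricted to OAHI of at least 1/h.** With f = 20%, 94 × 0.8 ≈ 75 per arm and the standard error is 8 × √(2/75) ≈ 1.31. With f = 40%, 94 × 0.6 ≈ 56 per arm and it is 8 × √(2/56) ≈ 1.51.

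**The case against.** The best reply is that children below 1/h are included on purpose. The Background says that long partial obstruction without discrete events can be the only form the disease takes. The section on neurocognitive associations groups snoring with mild OSA as linked to cognitive deficits. Recruitment strategy treats a positive questionnaire as a diagnosis in its own right, and the upper-limit-only rule is stated the same way in four places. On this view the population is consistent and only its label is loose.

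Much of this stands. It makes zero gain below 1/h a pessimistic assumption, which is why the half-gain column is shown. It is also true that the intention-to-treat contrast remains unbiased for the children randomised, and that OAHI is measured at baseline, so the share below 1/h can be reported. What does not stand is the label: criterion 3 requires confirmation on PSG, and the protocol's PSG scale gives OAHI below 1/h a different name. If inclusion is deliberate, the population is misnamed; if it is not, the criterion is incomplete.

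Two further inferences are tempting, and the document supports neither as a needed change.

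- **Minimisation.** A reader might want the lower level of "OSA classified as < 5 events/h or > 5 events/h by center" split at 1/h. Randomisation balances that split in expectation, the plan chose minimisation to avoid small cells, and the change would fall in an ongoing trial.
- **Questionnaire.** A reader might seize on "Questionnaire screening will ensure that children having PSG have high probability of OSA as this questionnaire has specificity of 0.87 for OSA", since specificity alone does not fix a predictive value. With perfect sensitivity (assumed) and the 3% upper prevalence in the Background, it would be 0.03 / (0.03 + 0.97 × 0.13) = 19%. But that is a general-population prevalence, and the children screened are referred for surgery. At an assumed 50% it is 0.50 / (0.50 + 0.50 × 0.13) = 88%. Every screened-in child then has PSG, so the sentence changes no result.

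**Conclusion.** The contradiction is in the text and depends on no assumption: Table 2 and three other places admit any OAHI below 10/h as mild-moderate OSA, while the severity scale starts mild OSA at 1/h. As written, the overall result applies to questionnaire-positive, surgery-suitable preschool children with OAHI below 10/h, including primary snorers. It is not specific to mild-moderate OSA.

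A reader might go further and say that the result cannot bear on mild-moderate OSA at all, or that the trial is underpowered. The document supports neither. Children with mild and moderate OSA are in the sample, and any loss of power depends on a share and a reduced benefit that the document does not give. Over the assumed range of 10 to 40%, power at 94 per arm would be 87 to 53% with no gain below 1/h and 90 to 78% with half the gain, against 93% without dilution. If few children fall below 1/h, or if they benefit as much as the rest, little or nothing is lost.

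**What to change.** Reconcile inclusion criterion 3 with the categories in Sleep study concordance. Which threshold should govern entry is for the investigators; this review does not choose one.

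If the present entry rule is kept:

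1. Restate the population in the Aims, Table 2 and the foreseen conclusion as symptomatic children with OAHI below 10/h, including primary snoring.
2. Report by arm the number and share with baseline OAHI below 1/h.
3. Before unblinding, prespecify the 12-month IQ contrast in children with baseline OAHI of at least 1/h as the supporting estimate for any statement about mild-moderate OSA. The primary analysis of all randomised children stays as it is. Baseline OAHI is measured before randomisation, so the subset is not affected by treatment.

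The cost is some rewording and one additional prespecified analysis, with no new data and no change to allocation. The overall result would carry a less favourable label, and the restricted estimate would be less precise: a standard error of about 1.31 or 1.51 points at an assumed 20% or 40% below 1/h, against 1.17 for all 94 per arm. Chosen after unblinding, the same analysis would be post hoc and could not carry that weight.

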#### Testing

Neurobehavioural (IQ) assessment after a hearing test (see exclusion criteria), PSG and medical review will be undertaken at baseline prior to randomization and repeated 12 months after randomization. Baseline testing also includes standardized history and medical examination and behavioral testing. The medical review will include family and personal histories of atopy, visual grading of tonsil size, measurement of body weight, height and calculated body mass index (BMI), and evening and morning blood pressure.

